**Figure 1. f1:**
[figure not shown]
Map of study sites in Yangon, Myanmar. Data Source: Ministry of Education, Myanmar.

**Table 1. T1:** Eligibility criteria.

	Inclusion criteria	Exclusion criteria
**Schools**	- High and middle schools in selected townships in Yangon. - Schools that have at least 40 6 ^th^ grade students. - Approval by headmaster of school through signed informed consent and Letter of Agreement. - Approval by relevant teachers by signed informed teacher consent.	- Schools with other ongoing dengue interventions. - Schools with classes with fewer than 40 6 ^th^ grade students - International schools not using the national curriculum and Burmese as language of instruction. - Boarding schools.
**Students**	- Students who will start 6 ^th^ grade in June Year 1. - Signed informed assent. - Signed informed consent by parents.	- Students who are seriously ill and not considered physically fit to participate. - Students whose parents do not provide consent.

### Interventions

The interventions consist of integrated sets of vector control and educational/knowledge transfer interventions that will be implemented simultaneously. The justification for implementing sets of interventions instead of single interventions is the growing consensus that single interventions are not sufficient to control vector borne diseases because of the complexity of the transmission systems and their components
^
37,
40
^. Vector control tools must also be integrated with educational interventions and knowledge transfer to achieve sustainable change. Interventions will be implemented in schools and communities by students and teachers with project staff overseeing the quality and coverage of the interventions as part of the process evaluations (see below). Interventions will commence at the start of the school year (June Year 1). No interventions will be implemented in the control arm. However, schools and communities may receive control activities carried out by the national dengue control program. These schools also receive standard dengue control instructions from the School Health Division.

The vector control intervention has four components: (1) Adult mosquito mass trapping using commercial oviposition traps (Gravid Aedes Trap (BG-GAT)
^
41
^ and locally produced traps (plastic bottles) constructed by students will be placed in both schools (10 per school) and a ample of 40 students’ households (one per household). Homemade traps will also be distributed to the communities by students. (2) Larval control using larvivorous guppy fish (
*Poecilia reticulata*). Guppy fish will be placed in suitable water storage containers in schools and households. Guppy fish production facilities (5 jars per school) will be set up in intervention schools, and students will learn how to manage these, propagate new fish, and distribute fish to their households and communities. (3) Prevention of mosquito breeding using tightly fitting lids or covers for water storage containers made of tarpaulin or other locally produced materials. These will be distributed to all intervention schools and 40 associated households per school. (4) Source reduction by weekly solid waste management and cleanup campaigns by students around their schools and households. This intervention require provision of garbage bags, protective gear and other material.

The education and knowledge transfer intervention has two components: (1) Dengue curriculum enhancement and capacity building for teachers, consisting of a participatory approach to transformative education. Teachers and representatives from the Ministry of Health and Sports (MOHS) and the Ministry of Education (MOE), together with the research team, will review the current school curriculum and teacher’s manual, identify potential entry points, and co-create new teachers’ manuals, lesson plans, and activities in line with the project’s focus on participatory, inquiry and place-based education
^
42,
43
^. This approach can be deployed to solve community problems by engaging students and school staff and combined with an adapted Communication for Behavioral Impact (COMBI)
^
25
^ strategy will contribute to knowledge diffusion from schools to communities and improvement of health education outcomes. Activities will cover theoretical sessions on dengue disease, entomology, biology, vector control, and ecology combined with extra-curricular practices, such as field studies on mosquito ecology, breeding habitats, and mapping; mosquito reproductive biology (life cycle) experiments; adult mosquito trap creation; guppy-mosquito predator-prey interaction experiments; and larvae and adult surveillance. The enhanced dengue curriculum will subsequently be evaluated by teachers and adapted accordingly to ensure applicability and sustainability. (2) Communication for behavioral change and transfer of knowledge. The COMBI-approach
^
25
^ will be adapted to the current school settings, which will result in the development of key messages and communication materials through a school-community collaboration. Science fairs and dengue days will be organized once a year to provide a platform for hands-on student experiments and projects, display acquired knowledge, and encourage knowledge and perception sharing between students, teachers, parents, and the wider communities. During the fairs, exhibition of vector control techniques, personal protection, student-led surveillance programs, and role-playing games involving students, parents, and teachers will be showcased to foster knowledge sharing and stimulate concerted actions for decentralized dengue surveillance and control. Community engagement will be carried out by students through school assignments and group work. Participatory epidemiology mapping activities and scenario building will be facilitated once per term where researchers, social science facilitators, teachers, and students collaborate on creating spatial representations of breeding sites and behaviors influencing transmission risk around the school areas. This will result in a map representing dengue epidemiological dynamics, as well as lead to the identification of a set of relevant, acceptable strategies for dengue prevention and control
^
44
^.

### Outcomes

The primary outcome is dengue incidence rates in communities (
Table 2)

**Table 2. T2:** Primary and secondary outcome measures and other outcomes. Baseline is June when school starts in Myanmar. (Y1=Year 1, Y2=Year 2).

Outcome	No.	Name	Index	Description	Unit	Frequency of data collection	Details
Primary outcome	1	Dengue incidence rate in communities	DI	Confirmed number of dengue cases (numerator) and the estimated population in each school catchment area (denominator) during study period	No. cases during study period / population	Continuous	Passive case detection assessed using dengue rapid diagnosis tests (RDT) in public hospitals and health centers
Secondary outcomes	2	Seroconversion rates in school children	SR _S_	Seroconversion rates between two time points in students at school	No. of seroconversions / no. observation-days	3 times: - Jun. Year 1 (baseline), - Oct. Year 1, - Feb. Year 2.	Seroconversion rates assessed by dengue rapid diagnosis tests (RDT)
	3	Seroconversion rates in households	SR _H_	Seroconversion rates between two time points in 20 households in communities	No. of seroconversions / no. observation-days	3 times: - Jun. Year 1 (baseline), - Oct. Year 1, - Feb. Year 2.	Seroconversion rates assessed by dengue rapid diagnosis tests (RDT)
	4	Mosquito adult index in schools	AI _S_	Mean number of adult female *Ae.* *aegypti* and *Ae. albopictus* per school collected indoors and outdoors	No. / school	4 times: - Jun. Year 1 (baseline), - Oct. Year 1, - Feb. Year 2, - Jun. Year 2.	Mosquito collections using a battery- driven mechanical aspirator.
	5	Mosquito adult index in households	AI _H_	Number of adult female *Ae. aegypti* and *Ae. albopictus* per school or house collected indoors and outdoors	No. / household	4 times: - Jun. Year 1 (baseline), - Oct. Year 1, - Feb. Year 2, - Jun. Year 2.	Mosquito collections using a battery- driven mechanical aspirator.
	6	Breteau index in schools	BI _S_	No. of *Aedes* positive containers per 100 schools	No. / 100 schools	4 times: - Jun. Year 1 (baseline), - Oct. Year 1, - Feb. Year 2, - Jun. Year 2.	Mosquito collections in schools
	7	Breteau index in households	BI _H_	No. of *Aedes* positive containers per 100 houses	No. / 100 houses	4 times: - Jun. Year 1 (baseline), - Oct. Year 1, - Feb. Year 2, - Jun. Year 2.	Mosquito collections in households

### Sample size

The required sample size was estimated based on the primary outcome, dengue incidence in communities. Since the numbers of dengue cases in each school catchment area were unknown, the sample size is necessarily an estimate. This estimate was attained by using township level data from the two selected study townships. There was a total of 2,885 dengue cases in South Dagon and Shwepyithar townships during 2013–2018 giving an average of 480 cases/year during this period. Dividing the number of cases with the number of middle and high schools in these two townships gives a conservative estimate of 480/46=10.5 cases per school catchment area per year. We plan to recruit a minimum of about 40 students per school per year. The calculations would assume that in the control, the incidence is 10.5 dengue cases per 40 person-years of observation i.e., incidence rate of 0.26 dengue cases per person-year of observation and expect this to drop to approximately 0.18 dengue cases per person-year of observation in the intervention (i.e., 7.35 dengue cases per 40 person-years of observation). Using a cluster randomized design with 46 schools (23 schools per arm) and 10.5 cases per school catchment area at baseline, with α=0.05 this study has more than 80% power to detect an approximate 30% reduction in the dengue incidence rates between the control and the intervention arms. This estimate assumed an intra-cluster correlation coefficient (ICC) of 0.01. An intra-cluster correlation coefficient (ICC) for the dengue outcome is not available in the literature. We therefore used the next best available estimates, based on our previous assessment of ICCs for malaria prevalence and incidence in Myanmar which are low in this country, on average 0.003 (95% CI 0.000-0.010)
^
45
^. Although malaria is a different vector-borne disease with different transmission pattens in different settings, we think that the ICCs for malaria in Myanmar probably are the most realistic we can get and provide better estimates than unfounded guesses. The ICC is context-specific (location, spatial scale, etc.) and is preferred for studies with binary outcomes, such as this trial. As an additional guide, a reduction in dengue incidence by 25–30% would be consistent with the objectives of both the WHO Global Strategy for dengue prevention and control 2012–2020
^
46
^ and the WHO Global Vector Control Response 2017–2030
^
37
^. Lack of data on adult mosquitoes in the study area precluded a sample size calculation for the quantitative secondary outcomes on adult mosquitoes. However, the number of adult mosquitoes in the area is expected to be large
^
47
^, thus giving substantial power to detect differences between the two arms. All 46 schools will be included in the study, using an equal cluster size of 23 schools per arm. Both arms (intervention and control) will be represented in each township. The power calculations were performed in Stata 16.

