### Study setting and participants

The study is planned to be conducted in South Dagon and Shwepyithar townships in Yangon Region, Myanmar (
Figure 1). These townships were selected out of the 45 in Yangon because of high dengue incidence and absence of other dengue projects. The population in South Dagon is ca. 307,000 and in Shwepyithar ca. 287,000. During 2013–2018 there were a total of 1,465 reported dengue cases (mean 244/year) and 15 deaths in South Dagon and 1,420 cases (237 cases/year) and eight deaths in Shwepyithar. These two townships represented approximately 12% of all reported dengue cases in Yangon Region during this period. There are 46 middle schools and high schools in these two townships, 20 in South Dagon and 26 in Shwepyithar. In 2019, there were an average of 250 sixth grade students per school. 40 high or middle schools will be included in the study (
Table 1). In each school approximately 40 sixth grade students (1–2 classes) will be selected based on feasibility, logistics, and willingness to participate. Each school and its catchment area (buffer zone) will be mapped. Non-overlapping school catchment areas that include students’ households represent the study clusters. Eligibility criteria are described in
Table 1. The delineation of school catchment area will consider mosquito flight distance from schools, but also providing sufficient buffer zones between adjacent catchment areas to avoid contamination between intervention and control schools. It is anticipated that a minority of students (<10%) will live in a different school catchment area within the two study townships. Due to the current health and security situation in Myanmar, the project has been terminated by the donor, but the protocol forms a basis for future implementation in Myanmar or elsewhere.

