### Data analyses

**
*Effect of intervention on primary outcome*
**

1. 
**Dengue incidence rate in communities (DI).** The total cumulative number of dengue cases in the communities will be recorded passively through patients presenting at collaborating public hospitals and health centers in the two townships. Each case will be confirmed by dengue antigen/antibody RDTs. Each case that resides in the school catchment areas will be noted as such. The denominator will be the estimated population in each school catchment area. Data analysis for the primary outcome will be a comparison of the overall difference in incidence rate of confirmed dengue cases between the intervention and non-intervention school catchment areas with sub-analyses comparing the monthly incidence over time, before, during and after the interventions to examine the timing of any intervention impact. Incidence data will be collected continuously over a one-year period. At the cluster level, analysis will be by intention to treat, i.e., taking the trial arm as that to which, each cluster was randomized. At the individual level, people will be taken to have the allocation of the arm in which they are resident at the time of any data contributed. A flowchart showing numbers of clusters, and average numbers of households per cluster, over time will be constructed in accordance with Consolidated Standards of Reporting Trials (CONSORT) guidelines
^
66

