*Aedes* mosquitoes were reduced in two community-driven integrated vector control interventions which included guppy fish, gravid-ovitraps, solid waste management, community education and engagement, and pyriproxyfen
^
74,
75
^. We believe that environmental risks, e.g., reduced biodiversity, of using guppy fish can be reduced by proper education on how to apply fish in containers in students’ homes. There is also an interesting educational component for students to understand biological concepts through fish breeding and development in school breeding aquaria.

Disease control interventions should be integrated and anchored in community processes, where schools could play important roles by engaging students, parents and teachers. By improving and/or adjusting school health curricula to include vector and disease control sessions, knowledge and behavioral change could be disseminated to communities by students
^
18,
76
^. Knowledge, attitudes, and self-efficacy of students for dengue prevention and control can be improved by using educational games, cartoons, observations, lectures and information campaigns
^
18
^. Since there is a lack of randomized controlled trials to assess the effect of school-based educational interventions on dengue and risk behaviors
^
18
^, our trial would contribute to this gap in knowledge. Health authorities in Myanmar are developing integrated training manuals and guidelines for community and school-based vector control, including the
*Aedes*-free school program
^
27
^.

Dengue transmission dynamics exhibit strong spatial and temporal variations
^
77–
79
^. Therefore, it is always difficult to assess the effect of dengue control interventions as they may fall in years with low and insufficient number of cases. Although we cannot predict future outbreak patterns, we have selected townships with the highest number of cases during the preceding years and where no other dengue interventions have been implemented. A longer intervention period would increase the likelihood of an outbreak year and avoid interepidemic periods, however, this will also reflect in costs and feasibility constraints. Another, limitation inherent in dengue research is the presence of relatively high proportions of asymptomatic cases, who, of course, will not show up in clinics and in national statistics.

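### The power calculation sets catchment-wide dengue cases over 40 students per school, so its clustering allowance does not belong to the unit analysed and the claim of more than 80% power is unsupported

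*Protocol article*

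**What the plan says.** The Sample size section bases the calculation on the primary outcome, dengue incidence in communities. It averages 2,885 township cases over 2013–2018 to 480 per year, and dividing by the number of schools "gives a conservative estimate of 480/46=10.5 cases per school catchment area per year". It then notes that about 40 students will be recruited per school and continues: "The calculations would assume that in the control, the incidence is 10.5 dengue cases per 40 person-years of observation". This yields 0.26 per person-year in control and about 0.18 under intervention (7.35 cases per 40 person-years). With 23 schools per arm and an ICC of 0.01, taken from malaria data, the conclusion is that "this study has more than 80% power to detect an approximate 30% reduction in the dengue incidence rates".

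The primary outcome is defined on another denominator. Under Data analyses, item 1: "The denominator will be the estimated population in each school catchment area". Table 2 says the same. Study setting and participants gives the population: "The population in South Dagon is ca. 307,000 and in Shwepyithar ca. 287,000".

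**The concern.** The numerator counts cases among all residents of a catchment. The denominator counts one small group of students. The resulting rate describes neither population and is about 320 times what the protocol's own case and population figures give.

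The practical question is whether this affects the power claim. It does so through clustering. The 40 fixes the cluster size, hence the design effect, and the rate of 0.26 fixes how much variation between catchments an ICC of 0.01 represents. Both change when the denominator becomes the catchment population. If incidence varies between catchments more than the calculation silently assumes, a true 30% reduction could well be missed. The protocol is offered as a basis for future implementation, so the calculation may be reused.

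**Working it through.** **Inputs.** Cases: 2,885 over six years (Sample size). Population: 307,000 + 287,000 = 594,000 (Study setting and participants). Clusters: 23 per arm; ICC 0.01; alpha 0.05; 30% reduction (Sample size). Follow-up: one year (Data analyses). Two-sided testing is assumed, because sidedness is not stated.

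**1. Reproducing the plan's figure.** Control rate 10.5/40 = 0.2625; intervention 7.35/40 = 0.18375. Design effect = 1 + (40 − 1) × 0.01 = 1.39. Effective n per arm = 23 × 40/1.39 = 662. As two proportions, SE = √[(0.2625 × 0.7375 + 0.18375 × 0.81625)/662] = 0.0228, so the difference of 0.07875 is 3.46 SE and power is 93%. With Poisson variance, power is 86%. The stated figure of more than 80% follows from the plan's inputs; the fault lies in the inputs.

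**2. The rate on the outcome's own denominator.** Cases per year = 2,885/6 = 480.8. Per school = 480.8/46 = 10.45 (480/46 is 10.43; the printed 10.5 is an immaterial rounding). People per school = 594,000/46 = 12,913, if catchments together cover both townships. Rate = 480.8/594,000 = 0.00081 per person-year, or 0.81 per 1,000. Ratio: 0.2625/0.00081 ≈ 324 (321 using 0.26).

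**3. What the ICC implies.** For a proportion p, k = √[ICC(1 − p)/p].
- At p = 0.2625: √(0.01 × 0.7375/0.2625) = 0.17.
- At p = 0.00081: √(0.01 × 0.99919/0.00081) ≈ 3.5.

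The same ICC thus describes very mild variation on the student denominator and extreme variation on the catchment denominator. It cannot be transferred from one to the other.

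**4. Power on the count scale.** With mean counts 10.45 and 0.7 × 10.45 = 7.32 per catchment, the variance of the difference is [(10.45 + 7.32) + k²(10.45² + 7.32²)]/23 = (17.77 + 162.8k²)/23, and the difference is 3.14. The normal test uses 1.96; the t test has 44 df. The values of k are assumptions, because the protocol gives none for dengue.

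| k | SE | Power, t test | Power, normal | Reduction detectable with 80% power (t) |
|---|---|---|---|---|
| 0 | 0.88 | 94% | 95% | 24% |
| 0.17 | 0.99 | 87% | 89% | 27% |
| 0.25 | 1.10 | 79% | 81% | 30% |
| 0.4 | 1.38 | 60% | 62% | 37% |
| 0.5 | 1.59 | 49% | 50% | 42% |

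Power reaches 80% only for k up to 0.245 (t) or 0.26 (normal). At the catchment rate, k = 0.25 corresponds to an ICC of 0.25² × 0.00081 ≈ 0.00005.

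**5. Coverage of the catchments.** The 10.45 assigns every township case to a catchment. Study setting and participants calls for non-overlapping catchments with buffer zones between them. If they held 60% or 80% of the cases (assumed), power at k = 0.25 would be about 64% or 73% by the t test.

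**The case against.** The strongest reply is that comparing event rates depends on the expected count per cluster and the variation between clusters, not on the size of the denominator. The section also states its design in those terms: "Using a cluster randomized design with 46 schools (23 schools per arm) and 10.5 cases per school catchment area at baseline". With no between-catchment variation power is 94–95%, and at the implied k of 0.17 it is 87–89%. This stands: the 320-fold discrepancy alone costs no power.

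A reader might go further and put ICC 0.01 on clusters of 12,913, giving a design effect of 1 + 12,912 × 0.01 ≈ 130 and power of about 5%. That reading is not supported. It implies k of about 3.5, and it takes a malaria ICC to a risk and cluster size for which nothing in the protocol justifies it.

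The evidence on heterogeneity is also thin. The Discussion says "Dengue transmission dynamics exhibit strong spatial and temporal variations", but names no scale. The only local comparison is between the two townships: 1,465/6/307,000 = 0.80 and 1,420/6/287,000 = 0.82 per 1,000 per year. Similar township averages do not show that catchments within them are similar, so neither a small nor a large k is documented.

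Finally, counts could exceed the historical ones, because the project supplies test kits and visits facilities monthly. With 20% more cases (assumed), power at k = 0.25 is 84%. So the direction of the error in the count is not settled. Buffer zones push it down and better detection may push it up.

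**Conclusion.** The denominator mismatch is real and plain from the protocol's own text. Its consequence is that the clustering allowance (ICC 0.01, 40 per cluster, design effect 1.39) does not apply to the catchments that will be analysed. The power claim holds if k is about 0.25 or less and fails above that; at k = 0.5 power is about one half. The protocol neither states nor defends a k, so the claim is unsupported. It is not shown to be false.

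Calling 10.5 cases conservative is likewise not established, since it rests on catchments capturing all township cases.

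A reader might infer that the trial's size and target effect lose their basis. They do not. The 46 schools are all the middle and high schools in the two townships, and the protocol separately ties a 25–30% reduction to WHO strategies. Nor can the count be called inflated because only test-confirmed cases at public facilities will be included: the protocol does not say how the historical cases were ascertained.

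These results assume two-sided testing, equal catchments, one year at the 2013–2018 average and, unless stated, full coverage of both townships. The planned Poisson or negative binomial analysis may give slightly different power from the t and normal approximations.

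**What to change.** Rewrite the sample-size paragraph:

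- Delete the 40 person-years and the rates 0.26 and 0.18.
- State the expected count as about 10.4 cases per catchment per year, on a catchment population of about 12,900 (about 0.81 per 1,000 person-years), and say that this assumes the catchments together cover both townships and capture all their cases. Let this assumption replace the word conservative, and note that buffer zones would lower the count.
- Replace the malaria ICC, which the section defends as suited to binary outcomes, with the between-catchment coefficient of variation k, which suits a count analysed by Poisson or negative binomial regression.
- Report power over an assumed range of k: about 87% at 0.17, 79–81% at 0.25 and 49–50% at 0.5. Give the corresponding detectable reductions: about 27%, 30% and 42%.
- Add a coverage sensitivity, for example 64–73% power at k = 0.25 with 60–80% of cases captured, marked as an assumption.

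The cost is one paragraph and a less favourable statement of power. The number of schools, the outcome and the analysis stay as they are.

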### Trial design

This cluster randomized controlled trial (RCT) is designed to study the effect of integrated entomological and educational interventions on dengue incidence, adult dengue mosquito density and KAPs regarding dengue risk reduction among students and parents in two townships in Yangon, Myanmar. The rationale for a cluster design is that interventions are area-wide in character, since they will be implemented in schools, rather than targeting individuals. It is not feasible to randomize some individuals within a school to one intervention and other individuals to another. Schools (clusters) will be randomized into an intervention arm and a control arm.

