*Ae. albopictus* (combined) per school or per house collected both indoors and outdoors for 15 minutes at each location (30 min total collection time) using a battery-driven mechanical aspirator. Collections will occur at baseline and once every four months in all schools. A negative binomial regression will be done with the number of mosquitoes as the outcome variable and number of school-visits as the exposure (denominator) variable, i.e., the logarithm of the number of schools as the ‘offset’. A logarithmic link function will be used. Hence, the exponential of the coefficient for arm will be the between-arm ratio in Adult Index (AI) according to the response variable used. Additional analyses of the AI
_S_ will be done by including the baseline value as an additional covariate. Due to the potential skewness of these values, this will be done by categorizing the index as zero, or above or below the median of the positive values.5. 
**Mosquito Adult Index in households (AI
_H_).** This is the same as AI
_S_ except that collections in households will be done for 10 minutes indoors and outdoors, respectively (20 min total collection time). Collections will occur at baseline and once every four months in five selected households per cluster. This index will be calculated and analyzed in the same way as AI
_S_.6. 
**Breteau Index in schools (BI
_S_).** The BI is the number of containers with
*Aedes* immatures/100 schools. It will be calculated at baseline as well as for each of the three follow up time points. This index will be analyzed similarly to the Adult Index.7. 
**Breteau Index in households (BI
_H_).** This BI is the number of containers with
*Aedes* immatures/100 houses. It will be calculated at baseline as well as for each of the three follow up time points. This index will be analyzed similarly to the Adult Index.8. 
**Knowledge, attitudes and practice scores in students (KAP

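### The claim of substantial power for the adult mosquito indices does not follow from large mosquito numbers: with 23 schools per arm, power depends on between-school variation, which the protocol never states

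*Protocol article*

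**What the plan says.** The Trial design section fixes the unit of randomization: "Schools (clusters) will be randomized into an intervention arm and a control arm". The Sample size section plans for all 46 schools, "using an equal cluster size of 23 schools per arm".

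For the primary outcome, the same section states an intra-cluster correlation, a control rate and a target effect. For mosquitoes it states none of these. It says: "Lack of data on adult mosquitoes in the study area precluded a sample size calculation for the quantitative secondary outcomes on adult mosquitoes". The next sentence gives the only ground offered, that "the number of adult mosquitoes in the area is expected to be large", and concludes: "thus giving substantial power to detect differences between the two arms".

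The Data analyses section plans a negative binomial regression for the Adult Index, with school-visits as the exposure. It adds a further analysis that includes the baseline index, categorised as zero or as above or below the median of the positive values because the index may be skewed. For households: "Collections will occur at baseline and once every four months in five selected households per cluster".

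**The concern.** The protocol says that power cannot be calculated, then asserts that it is substantial. The asserted reason concerns how many mosquitoes there are. In a trial that randomizes schools, the comparison of arms has two sources of variance. One is counting noise, which shrinks as catches grow. The other is the persistent difference between schools, which shrinks only with the number of schools. Abundance bears on the first and not on the second. The protocol accepts this logic for dengue, where it uses an intra-cluster correlation, and drops it for mosquitoes.

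Reducing entomological indices is the second specific objective, and lower mosquito indices are a stated hypothesis. If the adult indices show no significant difference, a reader who relies on the power statement could take that as evidence of no vector effect. The project has been terminated, but the protocol is offered for later use in Myanmar or elsewhere, so the sentence may be carried forward.

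**Working it through.** **The plan's own power figure.** Power is stated only for the primary outcome: "with α=0.05 this study has more than 80% power to detect an approximate 30% reduction". Inputs, taken as they stand in Sample size: "incidence rate of 0.26 dengue cases per person-year of observation" in the control arm (10.5/40 = 0.2625), 7.35/40 = 0.18375 in the intervention arm, 40 per school, 23 schools per arm, ICC 0.01.

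- Design effect: 1 + (40 − 1) × 0.01 = 1.39. Effective size per arm: 23 × 40 / 1.39 = 662.
- Comparison of proportions: power about 93%. Comparison of Poisson rates: 0.07875 / √(0.44625/662) = 3.03, so power is about 86%.

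The primary claim reproduces. There is no corresponding figure to reproduce for mosquitoes.

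**Inputs for the mosquito check.** From the protocol: 23 clusters per arm and α = 0.05. Assumed: a two-sided test, 80% power, the between-school CV, and the mean catch per school m in the control arm. The protocol gives neither CV nor m.

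**Variance of the comparison.** Let r be the ratio of the intervention mean to the control mean. On a scale where the control mean is 1:

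variance = [(1 + r)/m + CV²(1 + r²)] / 23

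As m grows without limit the first term vanishes. What remains is CV²(1 + r²)/23, which no number of mosquitoes reduces.

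**Smallest detectable reduction at unlimited catch.** With 1.96 + 0.84 = 2.80:

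- Rate difference: solve (1 − r) / √[CV²(1 + r²)/23] = 2.80 for r.
- Log scale: r = exp{−2.80 × √ln(1 + CV²) × √(2/23)}.

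Worked example on the log scale at CV 0.5: √ln(1.25) = 0.472 and √(2/23) = 0.295, so r = exp(−2.80 × 0.472 × 0.295) = 0.677, a 32% reduction.

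| Assumed CV | Log scale | Rate difference |
|---|---|---|
| 0.3 | 22% | 22% |
| 0.5 | 32% | 35% |
| 0.75 | 42% | 49% |
| 1.0 | 50% | 62% |

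Dividing by 22 instead of 23, as the Hayes–Bennett formula does, gives 36%, 50% and 64% at CV 0.5, 0.75 and 1.0. A negative binomial Wald test gives 34%, 46% and 56%.

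**How little the catch matters once it is moderate.** At CV 0.5 (rate difference), going from 20 mosquitoes per school to an unlimited number moves the detectable reduction only from 38% to 35%.

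**Power for a 30% reduction at unlimited catch.** The 30% is borrowed from the dengue outcome for illustration.

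- CV 0.4: 84–88%
- CV 0.5: 65–73%
- CV 1.0: 22–31%

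As a check, simulated gamma-Poisson counts with a t-test on school totals at CV 0.5 gave 60% power at a mean of 50 and 65% at a mean of 1,000. The Hayes–Bennett formula gives 60% and 63%.

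**Effect of baseline adjustment.** If the baseline index correlates 0.5 with follow-up (an assumption), the log-scale standard deviation is multiplied by √(1 − 0.25) = 0.866. At CV 0.5 the detectable reduction falls from 32% to 29%.

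**The case against.** The strongest reply is that an unsupported claim need not be false. A reader might infer from the table that the trial is underpowered for mosquitoes. The documents do not support that. Every figure rests on an assumed CV, and part of the plausible range is favourable: a 30% reduction is detectable with 80% power up to a CV of about 0.41, and a 50% reduction up to about 0.75 (Hayes–Bennett). The protocol sets no target reduction for mosquitoes, so failing at 30% would not be failing a stated aim. This objection stands, and it limits the point to the invalid inference.

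A reader might also take the planned negative binomial model, and the provision for zeros and skewness, as evidence that between-school variance is large. They are not. Over-dispersion can arise from visit to visit or within a school, and only the part that persists between schools forms the cap. The protocol does not say how large either part is.

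The plan also has three follow-up collections and a baseline-adjusted analysis, both of which can reduce the effective CV. The figures above are for an unadjusted comparison and would be pessimistic if the CV were read as that of a single visit. The cap becomes lower but does not disappear.

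On scope, the power sentence concerns adult mosquitoes. The Breteau indices face the same cap, but no power claim is made for them. It is also fair that these are secondary outcomes and that the analysis section commits to 95% confidence intervals where applicable, which partly guards against a null result being over-read.

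Finally, the choice of main model could be left to the later analysis plan. That is a reasonable view, but the protocol already ranks the adjusted model as additional, and the adjusted model is the available way to reduce the variance at issue.

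**Conclusion.** The point holds as a fault in a stated power claim. Large numbers of mosquitoes do not give substantial power when 23 schools per arm are randomized, and the quantity that decides the matter, the persistent between-school CV of the adult indices, appears nowhere in the protocol. Across assumed CVs of 0.3 to 1.0, the smallest reduction detectable with 80% power runs from about 22% to 50–62%, however many mosquitoes are caught. This rests on a two-sided 5% test, an unadjusted analysis and an equal CV in both arms. Whether the design is adequate cannot be settled from the document. The claim covers the school and household Adult Indices only, and the primary sample size is unaffected. The wording should be corrected; the design need not change.

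**What to change.** - Delete the sentence in Sample size that infers substantial power from mosquito numbers.
- In its place, state the minimum detectable rate ratio for the adult indices with 23 clusters per arm over a stated CV range, for example 0.3 to 1.0, and name the formula used.
- Update that statement with the between-school CV from the June Year 1 baseline collection. This comes before allocation according to Randomization and blinding, so it can be done without sight of any arm comparison.
- In Data analyses, make the baseline-adjusted negative binomial model the main adult-index analysis and keep the unadjusted model as supportive.

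The cost is wording in the protocol and analysis plan, and a less favourable power statement. The baseline data are already to be collected, so nothing is added to the fieldwork or to the number of schools. The gain from adjustment depends on the baseline correlation, and a three-category baseline will recover less than the illustration in which the full index is used.
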